Due to symptoms having a clinical similarity to posttraumatic stress disorder, it is suspected that interventions based on therapeutic approach for PTSD can be equally effective for secondary traumatic stress [22]. In national and international guidelines, exposition therapy approaches as first line treatment for posttraumatic stress disorder are recommended [23–27]. Among others, eye movement desensitization and reprocessing (EMDR) is a validated and effective treatment for PTSD [28]. While the underlying effect of bilateral eye stimulation is not fully understood [29], there is large evidence of EMDR effectively reducing symptoms of traumatic stress [30]. The planned study will examine the effectiveness of EMDR on secondary traumatic stress symptoms in a sample of interpreters working in refugee care. Therefore, a quasi-randomized controlled trial will be conducted, with a waitlist-control group to compare the development of symptoms of secondary traumatic stress in each group with and without EMDR intervention. The aim is to examine the hypothesis that EMDR intervention significantly reduces symptom burden of secondary traumatization compared to waitlist control.

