## Methods/design

To answer the research question if EMDR is more effective in reducing symptoms of secondary traumatization in adult interpreters caused by their work in refugee care settings than in a waitlist-control group, a quasi-randomized controlled trial (RCT) with an EMDR intervention of three to six sessions will be conducted. Primary outcome is the symptom burden of secondary traumatic stress symptoms measured with questionnaire for Questionnaire for Secondary Traumatization (“Fragebogen zur Sekundären Traumatisierung,” FST) [31]. Secondary outcomes are symptom burden of PTSD due to self-experienced traumatic events (assessed with Posttraumatic Diagnostic Scale [32]), depression (PHQ-9 [33]), anxiety (GAD-7 [34]), and somatization (SSD-12 [35]) as well as quality of life (SF-12), quality of professional life (PROQOL-5 [36]), and psychological wellbeing (WHO-5 [37]). The study is conducted with the aim of improving trauma-informed care and, more specifically, expanding the knowledge of trauma-confrontation techniques in the broader context of trauma-related disorders, as these have repeatedly proven to be effective [38, 39].

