### Primary outcome measure

The questionnaire-based data collection will be carried out upon the initial screening appointment (T1) for each group. For the intervention group, the second data collection point (T2) is around 6 weeks after T1, after the last session for the intervention, then 4 weeks (T3) and 8 weeks (T4) after T2. For the waitlist control group, T2 will be 6 weeks after T1, then after their last session (T3) and 4 weeks (T4) after T3. Also see Fig. 1. The participants will receive the link to the online questionnaires as well as reminders, if necessary, by email.

Secondary traumatic stress will be surveyed with the Questionnaire for Secondary Traumatization (“Fragebogen zur Sekundären Traumatisierung,” FST) [31]. This questionnaire surveys different symptoms of secondary traumatic stress based on diagnostic criteria of DSM-V for posttraumatic stress disorder, such as rumination, intrusions or nightmares, avoidance behavior, and, furthermore, cognitive or behavioral changes. The frequency of the above symptoms in the last week is assessed by 31 items on a 5-point Likert scale (1 = never, 5 = very often). From a sum score of ≥ 65, moderate secondary traumatic stress can be assumed. The structure of the questionnaire is similar to the Impact of Event Scale [40] and is designed to be used in professional context. It showed good internal consistency for the total score (Cronbach’s *α* = 0.94) in three different samples of professionals.

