### Randomization

Participants will be randomly assigned in either the intervention group or waiting list control group. Because of a rather small sample size, and to ensure seamless and reliable allocation for available therapists, this will be carried out through alternating allocation of participants at the initial screening interview for the study to avoid large differences in sample size. The allocation to one of the two groups is therefore already determined before inclusion in the study. Participants will be informed verbally at the time of the initial screening interview by the responsible therapist. Blinding is neither possible for the participant (as filling out of questionnaires during waiting time), nor for the EMDR therapist, as collaborative planning is necessary for the distribution of participants, as the therapists mainly work clinically. The team of EMDR therapists available to conduct the intervention comprises of five persons. Both groups will receive the same intervention that is planned as follows. A detailed participant timeline can be found in Fig. 2.

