### Intervention

Participants will be allocated to a therapist, medical doctor or psychologist of the department who will have completed, at least, EMDR training level 1. The EMDR treatment that will be carried out is comprised of 8 phases according to Shapiro [51]. In the first session, phases 1 and 2 will be conducted. The first phase includes the establishment of a therapeutic relationship as well as the exploration of the symptomatology and the trauma history. In this case, the therapist will comprehensively examine the symptoms of secondary traumatization including distressing situations relating to their work in refugee care in the present. Emotion regulation strategies of the participant will be elaborated. With help of the “adaptive information processing” model (AIP), the therapist and the participant will work out underlying stress situations from the professional context. According to the AIP model, traumatic memories, but also other “live events” or disturbing experiences that do not accord to the trauma criteria, can create a “pathogenetic memory.” These pathogenetic memories are stored in a dysfunctional way, are not connected to adaptive memory networks, and, subsequently, cause symptoms. Based on this assumption, repeated exposure to details of refugees’ traumatic experiences leads to dysfunctional storage of this experience of the affected interpreters [52, 53]. The therapist and the participant will carve out the respective distressing situations and classify them on a scale from 0 to 10 (subjective level of disturbance, SUD), as stated in the EMDR manual. Additionally, the participant will be introduced to the EMDR technique itself. An imaginative exercise, “safe place,” will be executed together and reinforced with EMDR technique. Techniques to stop flashbacks will be discussed. Additionally, the participant will receive a further imagination exercise, called “safe exercise,” that helps distancing oneself from disturbing thoughts. The first session takes 50–60 min. Phase 3–7 will be conducted in the following sessions according to the EMDR standard protocol. Phase 8 will be performed at the beginning of every exposition session. The EMDR standard protocol will be applied. This means that the disturbing memories will be worked on in a specific (“the first, the worst, the last”). However, by mutual agreement, the order in which the stressful memories are processed is left open to the therapist and the participant, if this leads to greater openness to therapy and adherence. Sessions will take place once a week; the therapist and participant will agree mutually on the date of the sessions, and they can be adapted to the participants’ needs. The confrontational sessions ends ideally when the SUD is 0. However, depending of the processed content, this cannot always be achieved, for example if the participant processes earlier stressful memories through so-called affect bridges. In this case, the session can be closed if SUD is not 0 but only reduced from the initial level. In this case, work on this memory will continue in the following session (phase 8). The processing time can differ between patients and takes around 60–90 min. A maximum of six sessions will be conducted. The number of sessions will be adapted to the participants needs. This implies that within the span of these six sessions, the stressful situations related to the participant’s work with refugees, which the participant seeks to address, are systematically managed. If a complete reduction of the SUD is not achieved within a single session, the issue may be resolved over 2–3 sessions. However, it is generally expected that each session is self-contained, as the nature of the underlying stressors suggests that a full reduction in SUD can be accomplished within one session. Consequently, the number of sessions corresponds to the number of specific situations requiring attention. Conducting fewer than six sessions does not imply that any therapeutic content is omitted. Participants in both groups receive the same intervention.

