### Statistical analyses

The quantitative data will be monitored and analyzed by the study team and colleagues of the research group using SPSS [55]. As the statistical evaluations are carried out by the study team with the support of the biostatistician, blinding is not performed. Baseline characteristics will be compared to assessed differences of the intervention and control group, especially regarding the symptom load of secondary traumatization symptoms as well as on the presence of self-experienced traumatic events and PTSD symptoms. The effectiveness of the EMDR intervention will be assessed using a piece wise growth curve model [56], a type of the latent growth curve model, based on the assumption that change of symptomatology along the study duration is not linear but depends to certain change points. In this model, growth rates between different time periods are compared. The main criterion of interest is the symptom load of secondary traumatic stress assessed with the FST. Further parameters to be analyzed are symptom load of depression, anxiety, and somatic distress as well as professional quality of life and quality of life. For the data collected, time periods of interest are before and after the intervention for intervention group (T1–T2) and waitlist control group (T2–T3), after the intervention to follow up for both groups (intervention group T2–T3/T4, control group T3–T4), and before and after the waiting period for the control group (T1–T2). Covariates will include current psychiatric treatment, current psychopharmacological prescription or medication change, and personal traumatic experience. The data of all randomized participants who filled out the pre-and post-questionnaires and, from the intervention group, who completed at least two sessions (one preparatory session with investigation of the experiences that will be processed (phases 1–2) and at least one confrontational session (phase 3–7/8) will be included in the analysis (per-protocol analysis). Reasons for incomplete participation in the intervention will be presented descriptively. With regard to the calculation of the sample size for a piece wise growth model, there is only scarce literature on how to do so [57]. Therefore, the sample size is calculated on the basis of analysis of variance (ANOVA) with repeated measures. According to literature, EMDR shows large effect sizes (*g* = 1.01 (CI 95% 0.42 to 1.62). For the present study, however, the effect size of EMDR on secondary traumatization is not known yet. Therefore, a conservative calculation with a medium effect (*d* = 0.5) was carried out. Assuming a type I error of *α *= 0.05 and a statistical power of 0.8, a sample size of *n *= 34 is calculated [58]. Assuming a drop-out rate of 18% [59], a sample size of 40 is aimed for. Missing data will be first identified and analyzed. No further measures will be carried out in case of missing data < 5%. If > 5% of the data are missing, it will be examined whether these are related to certain variables, such for example with symptom burden and whether patterns can be recognized. If these data are missing at random, no further procedures will be carried out. If missing values are systematically related to one of the recorded variables, a multiple imputation can be performed [60]. Due to a lack existing studies, the distribution of the data cannot be estimated. Therefore, the collected data is first checked for normal distribution and if not normally distributed transformed in order to carry out the analyses with transformed data.

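### The only analysis set is per-protocol with a session minimum for the EMDR group alone, which leaves the comparison with the waitlist open to bias, most likely in favour of EMDR

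*Protocol article*

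**What the plan says.** The hypothesis in the Background is that "EMDR intervention significantly reduces symptom burden of secondary traumatization compared to waitlist control". Allocation is by "alternating allocation of participants at the initial screening interview" (Randomization), so about 20 per group at the target of 40.

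The Statistical analyses section then fixes who is analysed: participants "who filled out the pre-and post-questionnaires and, from the intervention group, who completed at least two sessions". The two sessions are spelled out as one preparatory session and at least one confrontational session. The data of these people "will be included in the analysis (per-protocol analysis"; the bracket holds the only label given to the set. No as-allocated analysis and no sensitivity analysis on a fuller set is named. For the others, "Reasons for incomplete participation in the intervention will be presented descriptively".

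On timing, the Primary outcome measure section says: "For the waitlist control group, T2 will be 6 weeks after T1". That group's EMDR comes after T2. The Intervention section adds: "Participants in both groups receive the same intervention". No session minimum is stated for the waitlist group.

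On the number of sessions, Methods/design describes a trial "with an EMDR intervention of three to six sessions will be conducted", while the Abstract and the Intervention section give only a maximum of six.

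**The concern.** The session rule selects on something that happens after allocation, and in the T1-T2 comparison it can act on one arm only. An EMDR participant who stops after the preparatory session is deleted even if the T2 questionnaire comes back. A similar person on the waitlist, with the same prognosis and the same questionnaires, stays in. The two groups compared are then no longer the two groups allocated.

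The rule also changes the question. The hypothesis sets EMDR against waiting, but the analysis estimates the effect among those who reached a first confrontational session. The asymmetry continues after T2: the treatment-period slope of the EMDR group comes from people filtered on attendance, while the waitlist group's T2-T3 slope carries no stated attendance filter.

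Nothing else in the section restores those removed. Multiple imputation is optional and addresses missing values, not people taken out by the session rule. Because this is the sole set for the primary outcome, in an unblinded trial with alternating allocation, the result has little other protection.

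**Working it through.** **The plan's own figure.** Inputs from Statistical analyses: d = 0.5, alpha 0.05, power 0.80, repeated-measures ANOVA, drop-out 18%. Assumed, because not stated: f = d/2 = 0.25, two groups, m = 2 measurements, correlation 0.5, group-by-time interaction.

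- Noncentrality = f² × N × m / (1 − correlation) = 0.0625 × 34 × 2 / 0.5 = 8.5. Power is 0.807 at N = 34 and 0.781 at N = 32, so n = 34 is reproduced.
- 34 / 0.82 = 41.5, rounded up to 42. 34 × 1.18 = 40.1. The stated 40 is close to both.

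Neither figure depends on the analysis-set rule, and the point does not rest on them.

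**What the 18% is.** It is drop-out in the whole sample: 0.18 × 40 = 7.2 people. If all of them came from a 20-person EMDR arm, that would be 36% of the arm. The share of the EMDR arm below two sessions, called q here, is not given. The range below is assumed: q = 5%, 10%, 18% and 25% correspond to 1, 2, 3.6 and 5 people out of 20.

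**Case A: EMDR works, but only in those who reach confrontation.** Assume an effect of 0.5 SD in them and none in those excluded, with exclusion otherwise unrelated to outcome. As-allocated effect = 0.5 × (1 − q); the per-protocol estimate stays at 0.50; the gap is 0.5 × q.

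| q | As-allocated effect | Gap |
|---|---|---|
| 5% | 0.475 | 0.025 |
| 10% | 0.45 | 0.05 |
| 18% | 0.41 | 0.09 |
| 25% | 0.375 | 0.125 |

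**Case B: no true effect.** Null simulation with 20 per group, 100,000 runs and a t test on standardised change. In the EMDR arm only, people in the lowest share q of a latent score are removed; the score has correlation r with improvement. Expected bias = r × φ(z_q) / (1 − q), where φ is the standard normal density and z_q its q quantile. The multiplier is 0.195 at q = 10% and 0.320 at q = 18%. The chance of a significant result favouring EMDR should be 2.5%.

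| r | Bias, q = 10% | Chance | Bias, q = 18% | Chance |
|---|---|---|---|---|
| −0.5 (improvers leave) | −0.10 SD | 1.2% | −0.16 SD | 0.7% |
| 0 | 0 | 2.5% | 0 | 2.5% |
| 0.3 | 0.06 SD | 3.7% | 0.10 SD | 4.7% |
| 0.5 | 0.10 SD | 4.6% | 0.16 SD | 6.8% |
| 1.0 (exactly the worst leave) | 0.20 SD | 8.3% | 0.32 SD | 16.3% |

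The t test stands in for the planned piecewise growth model, so these rates show the order of size and do not predict the model's operating characteristics.

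**The case against.** Several stronger readings are tempting, and the document does not support them.

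- **That the comparison is biased towards EMDR as a matter of fact.** The direction is an inference. Case B gives zero when stopping is unrelated to outcome and a reversed sign when early improvers leave.
- **That the analysis keeps only those who tolerate EMDR.** The first session is preparatory. Someone who worsens or quits after one completed confrontational session stays in if the post-questionnaire is filled out. The rule removes people who never completed a confrontational session.
- **That the control group is unfiltered.** The questionnaire requirement applies to both groups. The plan also lists T2-T3 as the before-and-after treatment period for the waitlist, so it is not clear whether the post-questionnaire there means T2 or T3. What is one-sided is the session minimum.
- **That 18% of the EMDR arm would be lost.** That figure is overall drop-out. The two-session floor is low, and the session rule adds only those EMDR participants who returned the questionnaires but had fewer than two sessions. With one such person in 20, Case A gives a gap of 0.025 SD.
- **That acceptability can no longer be judged.** Reasons for incomplete participation and discontinuations are to be reported, and the Discussion treats use of the offer as its own point of interest.
- **That comparability secured by randomisation is lost.** Allocation alternates and is fixed before inclusion, so randomisation never secured it.

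All of this limits the size and certainty of the bias. It leaves the defect standing: one analysis set, an attendance rule on one side, and a hypothesis about EMDR against waiting. The article states the rule outright, so it is not a detail left to a fuller document.

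**Conclusion.** The point holds as a flaw in the analysis set. The primary comparison is open to bias, and favour towards EMDR is the most plausible direction: those removed had no completed confrontational session and cannot show its benefit, avoidance is part of the condition, and the protocol itself expects a short-term rise in stress from the procedure.

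Confidence is high for the defect and much lower for its size. The gap is about 0.03-0.13 SD if EMDR truly works at d = 0.5 and 5-25% of the arm is excluded without benefit; this is a difference in the effect estimated, not a false positive. With no true effect, 10-18% excluded and a correlation of 0.3-0.5 with poorer change, the false benefit is about 0.06-0.16 SD and the chance of a false result favouring EMDR is 3.7-6.8% instead of 2.5%. Both the excluded share and its link to outcome are assumptions, and with few exclusions the effect could be near zero.

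A secondary point: the planned range of three to six sessions, the bare maximum of six and the two-session analysis minimum do not line up. An analysis minimum need not equal the planned range, so this is a matter of reconciliation and not a second source of bias.

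**What to change.** 1. Make the primary analysis all allocated participants in their allocated group, whatever number of sessions they attended, using every available FST value by maximum likelihood in the planned growth model, which can take incomplete series.
2. Keep sending the questionnaire links and reminders to people who stop treatment, in both groups.
3. Report the two-session per-protocol set as a labelled sensitivity analysis, and state which time point counts as the post-questionnaire in each group.
4. Give the number below two sessions in the EMDR group, so that readers can place the result in the ranges above.
5. Reconcile the session numbers in the Abstract, Methods/design, Intervention and Statistical analyses sections.

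The cost is a change of wording and some further reminders. The stated 34 and 40 need not change. The downside is a somewhat diluted estimate: under Case A, 0.45 in place of 0.50 if 10% of the EMDR arm stops before confrontation.

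### The stated 80% power with n = 34 does not apply to a 0.5-SD difference between EMDR and waitlist: the simple routes to 34 power either a 1.0-SD group difference in change or a within-person change

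*Protocol article*

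**What the plan says.** The Background sets the hypothesis as a between-group one: "EMDR intervention significantly reduces symptom burden of secondary traumatization compared to waitlist control". Methods/design repeats it as a comparison with a waitlist-control group. Under Statistical analyses the planned model is a piecewise growth curve. Because guidance on sizing such a model is scarce, "the sample size is calculated on the basis of analysis of variance (ANOVA) with repeated measures". The article cites a literature effect ("EMDR shows large effect sizes (*g* = 1.01 (CI 95% 0.42 to 1.62"), notes that the effect on secondary traumatization is unknown, and chooses a smaller one: "Therefore, a conservative calculation with a medium effect (*d* = 0.5) was carried out". The result is: "Assuming a type I error of *α *= 0.05 and a statistical power of 0.8, a sample size of *n *= 34 is calculated". Then: "Assuming a drop-out rate of 18% [59], a sample size of 40 is aimed for". Allocation is by alternation ("alternating allocation of participants at the initial screening interview for the study to avoid large differences in sample size"), so 34 means 17 per group. The analysis set is per-protocol, so drop-outs are lost to it. The article does not say which ANOVA effect was powered, how many measurements entered, or what within-person correlation was assumed.

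**The concern.** A standardized difference of 0.5 between two groups of 17 is far from 80% power in an ordinary two-group comparison, where 64 per group are needed. Repeated measures can reduce that number, but only through the correlation between measurements, which is not given. The question is whether any simple repeated-measures calculation yields 34 and also addresses EMDR versus waitlist at 0.5 SD.

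If none does, the protocol promises sensitivity to a medium effect that the design does not have. A non-significant result could then be taken as evidence against such an effect, although the trial would more often than not have missed it unless the correlation is high.

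**Working it through.** **Inputs.** From the article: d = 0.5, alpha 0.05, power 0.8, N = 34 (17 per group), 18% drop-out, 40 enrolled. Assumed because not stated: two-sided testing, two measurements (T1 and T2, the only pair before the waitlist group is treated), and correlation rho, shown over 0.3 to 0.8.

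**Reproducing 34.** For a repeated-measures ANOVA interaction with m measurements, the noncentrality is lambda = N x m x f² / (1 - rho). With f = d/2 = 0.25, m = 2 and rho = 0.5, lambda = 34 x 2 x 0.0625 / 0.5 = 8.5. The noncentral F on 1 and 32 degrees of freedom gives power 0.807, and 34 is the smallest even N that reaches 0.80. With m = 3 or 4 the answer would be 28 or 24.

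A paired t-test at d = 0.5 with n = 34 gives 0.808, and 34 is again the smallest n. The time effect in the ANOVA with the same inputs also returns 34.

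Routes that do not return 34 (total N): two-sample t at d = 0.5, 128; between-group main effect with m = 2 and rho = 0.5, 98.

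**What f = 0.25 means in the interaction.** In a 2 x 2 interaction each of the four cell means deviates by f SD, with alternating sign. One group's change then differs from the other's by 4 x f = 4 x 0.25 = 1.0 SD. At rho = 0.5 the SD of change is sqrt(2 x (1 - 0.5)) = 1 raw SD. As a check, a two-sample t-test on change scores with 17 per group and a 1.0-SD difference gives the same 0.807. A 0.5-SD difference in change corresponds to f = 0.5/4 = 0.125, for which N = 34 gives 0.293 and 80% power needs N = 128.

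**Power for a 0.5-SD group difference, 17 per group.** The effect on the test scale is 0.5 / sqrt(2(1 - rho)) for change scores and 0.5 / sqrt(1 - rho²) with baseline adjustment. The noncentral t gives:

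| rho | change score | baseline-adjusted |
|---|---|---|
| 0.3 | 0.22 | 0.32 |
| 0.5 | 0.29 | 0.37 |
| 0.7 | 0.45 | 0.51 |
| 0.8 | 0.61 | 0.65 |

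**Correlation needed.** With 17 per group, 80% power requires 0.99 on the test scale. For change scores, 2(1 - rho) = (0.5/0.99)² = 0.255, so rho is about 0.87. With baseline adjustment, 1 - rho² = 0.255, so rho is about 0.86.

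**Drop-out.** 34 / (1 - 0.18) = 41.5, so 42. Enrolling 40 leaves 40 x 0.82 = 32.8. Under f = 0.25 and rho = 0.5, power at N = 32 and 33 is 0.78 and 0.79.

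**The case against.** The article leaves the software settings unstated, as condensed protocols often do, so how 34 was obtained is an inference. A reader might conclude that the authors wrongly converted d to f by halving it. The document does not establish that. The paired route gives 34 without any conversion, and within-group periods before and after treatment are among those the article lists as of interest. This stands, and the finding does not need to choose: neither route powers the comparison with waitlist at 0.5 SD.

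A reader might also take true power to be about 30% to 40%. That holds only at a correlation of 0.5, which the document never gives. If d is standardized by the raw SD, a higher correlation raises power; if by the SD of change, 0.29 applies whatever the correlation.

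It is tempting to add that the trial is really sized for the literature effect of 1.01. The numbers are close, but the article does not say whether that value standardizes post-treatment scores or change, so equating them is unsupported.

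The ANOVA is also a stand-in. The planned growth model uses up to four time points and the waitlist group's own treatment phase. A simple version (common T1 mean, equal correlations, treatment change minus waiting change, N = 34) gives power for 0.5 SD of about 0.40, 0.54 and 0.69 at correlations 0.5, 0.7 and 0.8. For 1.0 SD it gives about 0.93 at correlation 0.5. So the ANOVA figures are not the planned model's power, but this version also stays below 80% for 0.5 SD.

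Finally, the Discussion already names too few participants as a possible limitation. It does not say that the power statement itself is off.

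**Conclusion.** The concern holds for the power statement as written. For the hypothesis in the Background, 34 completers give 80% power under repeated-measures ANOVA for a group difference in T1-T2 change of about 1.0 SD at correlation 0.5, not 0.5 SD. At 0.5 SD, power is 0.22 to 0.61 on change scores and 0.32 to 0.65 with baseline adjustment over correlations 0.3 to 0.8. The stated figures fit the stated comparison only if the correlation is about 0.87. Calling the calculation conservative is therefore not justified.

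This rests on two-sided testing, 17 per group, two measurements and no loss of participants. The drop-out slip is real but minor: two participants, and power of 0.78 to 0.79 instead of 0.80 for the 1.0-SD effect. That the authors multiplied 34 by 1.18 (40.1) is a plausible guess, not something the article shows.

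**What to change.** Rewrite the sample-size text without changing enrolment:

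- Name the ANOVA effect tested, the number of measurements and the correlation assumed.
- State that 34 completers give 80% power for a between-group difference in T1-T2 change of about 1.0 SD at correlation 0.5. Give the power for 0.5 SD across the range of correlations, and note that these figures belong to the ANOVA approximation, not to the piecewise growth model.
- Delete the word conservative.
- State that 40 enrolled leaves 32 to 33 completers at 18% drop-out (42 would be needed to leave 34).
- Report the between-group effect with its 95% confidence interval, and say in advance that a non-significant result does not exclude a medium effect.

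Baseline information is worth using, but T1 FST should not be added as a covariate to a growth model in which T1 is already an outcome. Use it within the model, for example through a common T1 mean across groups, or in a supplementary ANCOVA.

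The cost is rewording and a less favourable power statement. Using baseline information is a small analysis decision, to be fixed before the data are analysed. No further participants are required.

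### The missing-data rule contradicts itself and leaves imputation optional, and the completer-only analysis set removes intervention participants without a T2 questionnaire before the rule can apply

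*Protocol article*

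**What the plan says.** All of this is in the Statistical analyses section of the protocol article.

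- **Threshold.** Below 5% missing, nothing is done. Above 5%, "it will be examined whether these are related to certain variables, such for example with symptom burden".
- **First branch.** "If these data are missing at random, no further procedures will be carried out".
- **Second branch.** "If missing values are systematically related to one of the recorded variables, a multiple imputation can be performed".
- **Analysis set.** "The data of all randomized participants who filled out the pre-and post-questionnaires" are analysed, with a further condition for one arm only: "from the intervention group, who completed at least two sessions". The plan labels this per-protocol and states no other set.
- **Model and size.** The model is a piecewise latent growth curve for the FST. The target is 40 participants, allowing for 18% drop-out. The analysts are not blinded.

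Which time point counts as post is not fixed for the waitlist arm. The Statistical analyses section gives T2–T3 as that arm's before/after-treatment interval and T1–T2 as its waiting period. The last sentence of the Quality of life section sets T1 against T2 and T3 without separating the arms.

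**The concern.** In standard usage, data are missing at random when missingness depends on recorded variables. On that meaning the second branch describes the same case as the first, yet one says to do nothing and the other permits imputation. An analyst cannot follow both.

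The analysis set makes this worse. A growth model fitted by likelihood can use the T1 score of someone who later drops out, and is then valid under missing at random without imputation. Restricting the data to people "who filled out the pre-and post-questionnaires" discards that score.

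At stake is whether the primary contrast rests on a self-selected subset with no correction, and whether the choice to correct is made by unblinded analysts after seeing the data.

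**Working it through.** **1. The two branches side by side.**

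| Meaning given to the first branch | Situation it covers | Action | Second branch |
|---|---|---|---|
| Standard: missing at random | Missingness depends on recorded variables | None | Same situation, imputation allowed: contradiction |
| Loose: missing completely at random | Missingness unrelated to recorded variables | None | Different situation, imputation allowed but not required |

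The second row is coherent in direction. It is still not binding.

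**2. The threshold.** The text covers less than 5% and more than 5%. Counted over 40 participants, 2/40 = 5.0% falls in neither branch and 3/40 = 7.5% is the first count above it. Expected drop-out is 0.18 × 40 = 7.2, so about 7 people, well above the threshold. This leaves 40 × 0.82 = 32.8 completers.

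**3. The association check.** Assume 40 participants, about 18% missing, and a two-sided t-test at 0.05 of T1 FST by missingness. Drop-out is driven by a latent score with a set correlation to T1. By simulation:

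- correlation 0.5 in both arms: power about 58%;
- correlation 0.5 in one arm, 0 in the other: power about 19%;
- correlation 1.0 in both arms: power above 99%.

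The check is weakest for moderate one-arm dependence, which is a case that biases the group contrast.

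**4. Order of operations.** For the intervention arm, the post-treatment questionnaire is T2. A participant without it fails the entry condition, so the rule never meets that missing score. In the waitlist arm this is so only if post means T2. If it means T3, someone with T1 and T3 but no T2 stays in and the rule could act. In both arms the rule can still act on missing items, covariates and follow-up scores.

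**5. Illustrative size.** From the protocol: drop-out 18%, planning effect d = 0.5. Assumed: T1 and T2 bivariate normal with SD 1 and correlation ρ of 0.5 or 0.7; in one arm the 18% with the highest latent score drop out, that score correlating λ with T1; in the other arm drop-out is unrelated to T1.

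- The 82nd normal percentile is z = 0.915, with density 0.2624.
- The completers' T1 mean shifts by −λ × 0.2624/0.82 = −0.32λ SD.
- Their T2 mean shifts by ρ times that, so mean change is biased by +0.32λ(1 − ρ).

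| | ρ = 0.5 | ρ = 0.7 |
|---|---|---|
| λ = 1.0 | 0.16 SD | 0.10 SD |
| λ = 0.5 | 0.08 SD | 0.05 SD |

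Against d = 0.5 this is 0.16/0.5 = 32% at most and 0.05/0.5 = 10% at least.

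**6. Cross-check.** A separate simulation (300,000 per arm, true effect −0.50 SD, 18% missing in each arm) used logistic drop-out on T1 with slope 1 per SD in the intervention arm only.

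| Contrast | ρ = 0.5 | ρ = 0.7 |
|---|---|---|
| Completers, change | −0.42 | −0.45 |
| Completers, T2 score only | −0.58 | −0.61 |
| All T1 scores kept (likelihood or imputation) | −0.50 | −0.50 |

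The direction of the bias depends on the contrast. When both arms had the same drop-out mechanism, or drop-out was completely at random, completers also returned −0.50.

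**The case against.** **The rule is backwards.** A reader might infer that the plan acts when it need not and stays idle when it should act. The text does not support that. Setting at random against systematically related suggests that the authors meant completely at random, and then the order is the usual one. What stands is a wrong label and a non-binding action.

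**Doing nothing under missing at random means complete cases.** This does not follow from the quoted sentence either, because a likelihood-fitted growth model needs no imputation there. The entry condition on questionnaires takes that protection away. The objection therefore moves the fault from the rule to the analysis set, but does not remove it.

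**The rule can never reach a missing T2 score.** This is firm only for a wholly missing questionnaire in the intervention arm, as shown in step 4.

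**The size is hypothetical.** This is correct. The protocol names symptom burden only as an example of what will be examined and does not say that it predicts drop-out. The correlations and the one-arm mechanism are assumptions. The bias comes from the completer set rather than from the mislabelled sentence. The session requirement in one arm makes selection that differs by arm plausible, but does not establish it.

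**Detail belongs in an analysis plan.** This is fair for a list of imputation predictors or a sensitivity analysis for data missing not at random, and neither is asked for here. It does not excuse a rule that the article states and that conflicts with itself.

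**Conclusion.** The concern holds in limited form and should be fixed. The missing-data rule is mislabelled and self-contradictory. On its most favourable reading it still leaves imputation to discretion, relies on a check with limited power at this sample size, and has a gap at exactly 5%. The stated analysis set removes intervention participants without T2 before the rule applies. For the waitlist arm, that turns on an undefined post time point.

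The plan's own 18% means that about 7 of 40 people may be affected. A bias of 0.05 to 0.16 SD in the completer difference in change is an illustration under one-arm dependence of drop-out on T1 FST and a T1–T2 correlation of 0.5 to 0.7. It is not a forecast, and it is zero if both arms lose people in the same way.

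**What to change.** - Delete the 5% threshold and the step that tests for an association before choosing a method.
- Fit the primary piecewise growth model by (restricted) maximum likelihood to every available FST value from every allocated participant, including those with T1 only. Alternatively, make multiple imputation mandatory.
- Use the terms missing completely at random and missing at random in their standard senses, and say which one the primary analysis assumes.
- Define the post time point for each arm.
- Keep the completer set with the two-session condition as a per-protocol sensitivity analysis.

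The cost is a revised paragraph and a little extra analysis. SPSS, the package named in the plan, has mixed-model and imputation procedures, and no new data are needed.
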